### Sample size considerations

Sample size and power calculations were performed for the main outcome of interest – change in systolic BP (sBP) after 1 year due to each intervention individually – using effects sizes and standard deviations from multiple published trials of interventions to improve BP control. Baseline data among patients with CKD in the San Francisco Health Network demonstrate an average sBP of 151 mmHg (range: 140–160) across primary care providers, with an intra-class coefficient = 0.0008. Thus, we used simple *t*-test calculations to determine power analysis. Using a two-tailed alpha of 0.05 and beta of 0.8, we need to enroll 200 patients to each intervention (CKD-ATSM vs. usual care and CKD-registry vs. usual care) to detect a 6-point change in systolic BP. This is similar to that achieved by previous team-based intervention trials [42]. Using an interaction analysis, we will also be able to detect a 12-point difference in systolic BP between the arm that receives no intervention and the arm that receives both interventions. To account for a 10 % loss to follow-up, we will need to enroll 220 patients to each intervention, or 110 patients to each arm of the 2x2 factorial design.

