### Enrollment and randomization

#### Providers

Consistent with the patient-centered medical home, clinicians in participating primary care clinics are assigned to practice teams responsible for distinct panels of patients. Each team consists of several physicians, nurses, nurse practitioners, medical assistants and behaviorists. Within each clinic, patient demographics across practice teams are similar with respect to race/ethnicity, gender, age and language distribution. To minimize contamination among clinicians, practice teams, rather than primary care providers, are randomized to receive the CKD registry or to receive usual care.

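### The 80% power for a 6-point systolic BP effect is not supported for the registry, because it rests on a patient-level t-test and a provider-level ICC while practice teams are randomised

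*Protocol article*

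**What the plan says.** Sample size considerations (Protocol article) reports an average baseline systolic BP of 151 mmHg "across primary care providers, with an intra-class coefficient = 0.0008". From this it infers that simple t-test calculations suffice. The result is one systolic BP figure for both factors: "we need to enroll 200 patients to each intervention (CKD-ATSM vs. usual care and CKD-registry vs. usual care) to detect a 6-point change". The error rates are given as "Using a two-tailed alpha of 0.05 and beta of 0.8". No SD is printed, only its source: "using effects sizes and standard deviations from multiple published trials of interventions to improve BP control". After a 10% allowance for loss, "we will need to enroll 220 patients to each intervention, or 110 patients to each arm of the 2x2 factorial design".

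The two factors are not randomised in the same way. Under Enrollment and randomization, the Providers paragraph says that "practice teams, rather than primary care providers, are randomized to receive the CKD registry or to receive usual care", and that each team includes several clinicians. The Patients paragraph allocates CKD-ATSM to individuals, blocked and stratified within provider. Study design, by contrast, says that primary care providers are randomised to the registry. Data analysis plans generalized estimating equations with robust standard errors clustered by provider. It does not mention the team.

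**The concern.** A low ICC across providers is offered as the reason to ignore clustering for both comparisons. For CKD-ATSM this does no harm, because treatment varies within provider. For the registry it leaves two gaps. First, the cluster that shares the intervention is the team, and the outcome is one-year change under a team-delivered intervention, whereas the ICC quoted is for baseline BP across providers. Second, even a negligible ICC does not change the number of randomised units. A comparison of teams that estimates between-team variation has degrees of freedom set by the number of teams, not by some 400 patients.

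The registry is one of the trial's two factors. If its result is null, readers will judge it against a claimed 80% power for 6 mmHg. If the real power was nearer 65% or 70%, the null would be taken as stronger evidence of no effect than the design can give.

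**Working it through.** **Inputs.** From Sample size considerations: two-sided alpha 0.05, power 0.80 (printed as beta), difference 6 mmHg, 200 v 200 evaluable for each factor, ICC 0.0008. Not in the article, and so assumed: the SD, the number of teams K, and any ICC other than 0.0008.

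**1. The plan's own figure.** The 200 cannot be reproduced without an SD, so I solved for the SD:

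SD = 6 / [√(2/200) × (1.960 + 0.842)] = 6 / (0.1 × 2.802) = 21.4 mmHg (21.36 with the t distribution).

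At SD 21.4 the standard formula returns 200 per level, so the figure is coherent. On this reading it is sized for exactly 80% under independence and has no margin for clustering. Read literally, a beta of 0.8 means 20% power, which needs only about 32 per level at this SD. The 0.8 is therefore power.

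**2. Loss to follow-up.** 220 × 0.9 = 198 per level, or 396 in all. Using 396 instead of 400 changes the powers below by less than 1 point.

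**3. Registry at team level.** With m = 400/K patients per team:

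- design effect DE = 1 + (m − 1) × 0.0008
- SE = 21.42 × √(2 × DE/200)
- noncentrality = 6/SE
- power from the noncentral t with K − 2 df

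Example, K = 8: m = 50, DE = 1 + 49 × 0.0008 = 1.039, SE = 2.142 × √1.039 = 2.184, noncentrality 2.748, critical t (6 df) 2.447, power 63%.

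| Teams (assumed) | DE | SE | Power, DE only (normal) | Power, K − 2 df | Same df, ICC 0 |
|---|---|---|---|---|---|
| 8 | 1.039 | 2.184 | 78.5% | 63.2% | 64.9% |
| 12 | 1.026 | 2.170 | 79.0% | 70.3% | 71.4% |
| 20 | 1.015 | 2.158 | 79.4% | 74.9% | 75.5% |
| 30 | 1.010 | 2.153 | 79.6% | 76.8% | 77.2% |

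Over 6 to 40 teams the design effect alone gives 78.0% to 79.7%. The drop comes almost wholly from the degrees of freedom, as the ICC 0 column shows.

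**4. In mmHg.** The noncentrality that gives 80% power is 3.366, 3.111, 2.961 and 2.904 for 6, 10, 18 and 28 df. Multiplied by the SEs above, the difference detectable with 80% power is about 7.35, 6.75, 6.39 and 6.25 mmHg for 8, 12, 20 and 30 teams, against the stated 6.

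**5. Sensitivity to the SD (ICC 0.0008, K − 2 df).**

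| SD (assumed) | 8 teams | 12 teams | 20 teams |
|---|---|---|---|
| 20 | 69.1% | 76.1% | 80.4% |
| 18 | 77.7% | 84.2% | 87.8% |

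**6. Sensitivity to the ICC (SD 21.4, K − 2 df).** These values are illustrative and have no source in the article. At 0.01, power is 48.7%, 59.4%, 68.1% and 72.3% for 8, 12, 20 and 30 teams. At 0.02 it is 38.8%, 50.5%, 61.7% and 67.8%.

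**The case against.** - **The ICC is tiny at team level too.** Providers appear to be nested in teams, so the between-team share of baseline BP variance should not exceed the between-provider share, apart from estimation error. This stands for baseline BP and is why the design effect costs at most about 2 points. It does not settle the ICC of one-year change, and it does not touch the degrees of freedom.
- **The SD is inferred.** 200 is a round number and may include some margin. This stands: at SD 20 with 20 teams, power is back at 80%. With 8 teams it stays below 80% at every SD from 18 to 21.4.
- **K − 2 df is not the planned reference.** The analysis clusters by provider and adjusts for age, clinic and language. If team-level variance were exactly zero, a patient-level test would be valid and would have nearly its stated power. The K − 2 df are the price of not assuming that. Covariates may recover some power: an assumed 15% cut in variance at SD 21.4 gives about 81% with 20 teams. Adjusting for clinic would, however, use up some team-level degrees of freedom.
- **A condensed article need not give the number of teams or the SD.** Agreed, and their absence is not the point. The point is the stated step from a provider-level ICC to a t-test for a factor randomised by team.

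A reader might go further and infer that the registry definitely lacks 80% power, or that the quoted ICC by itself removes it. The article supports neither. The first depends on three quantities it does not give, and the second is contradicted by the design-effect column.

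**Conclusion.** The claim of 80% power for 6 mmHg is unsupported for the registry and probably too high. It is not shown to be false. At the implied SD of 21.4 mmHg and the article's own ICC, inference on team-level degrees of freedom gives roughly 63% to 77% for 8 to 30 teams. That range assumes 200 per level was set for exactly 80% power, equal team sizes, no covariate gain, and a team-level ICC of change equal to 0.0008. A larger ICC would lower it. An SD of 20 or less with 20 or more teams would bring it to 80% or above.

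The figure of about 80% for CKD-ATSM is not affected. The conflict between Study design (providers randomised) and the Providers paragraph of Enrollment and randomization (teams randomised) is a separate, documented inconsistency. It decides which cluster the registry calculation must use.

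**What to change.** Keep the sample size and rewrite the sample-size paragraph by factor:

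1. For CKD-ATSM, keep about 80% power for 6 mmHg and state the planning SD.
2. For the registry, give power or the detectable difference at team level, using the actual number of teams, the same SD, DE = 1 + (m − 1) × ICC and team-based degrees of freedom. Show a range of ICCs for one-year change, for example 0.001 to 0.02, labelled as assumptions.
3. Make Study design and Enrollment and randomization agree on whether teams or providers are randomised to the registry. If it is teams, have the registry analysis reflect the team as the cluster.
4. Replace beta of 0.8 by power of 0.8 (beta 0.2).

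The cost is a reworded paragraph, one consistency edit, a check of the clustering level in the analysis, and probably a less favourable registry figure. No extra patients are needed.

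### Sample size paragraph: 'beta of 0.8' should read power 0.80, and, separately, 220 per intervention leaves 198 rather than 200 after the stated 10% loss

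*Protocol article*

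**What the plan says.** All the figures are in the section on sample size considerations of the protocol article.

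- Error rates: "Using a two-tailed alpha of 0.05 and beta of 0.8".
- Target difference: the calculation is meant "to detect a 6-point change in systolic BP" at one year, for each intervention separately.
- Base size: 200 patients for each intervention.
- Method: "Thus, we used simple *t*-test calculations to determine power analysis". The reason given is a very small intra-class coefficient, so no design effect is applied.
- Variability: the calculation was done "using effects sizes and standard deviations from multiple published trials of interventions to improve BP control". The SD itself is not printed.
- Loss allowance: "To account for a 10 % loss to follow-up", the section continues, "we will need to enroll 220 patients to each intervention", which it equates to 110 in each of the four arms.

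The 110 per arm settles what the 200 and 220 count. Each level of a factor in the 2x2 design is made up of two arms, so 220 is the number per level of each intervention, and total enrolment is 4 × 110 = 440.

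**The concern.** Two statements in the paragraph do not fit the calculation they describe.

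The first is a label. Beta is the probability of missing a true effect. A beta of 0.8 therefore says the trial has a 20% chance of detecting 6 mmHg. Since the SD is not printed, a reader cannot recover the intended power from the other inputs alone, so the label has to be right.

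The second is the loss allowance. To have a given number left after a proportion d is lost, the number needed is divided by 1 − d. Multiplying by 1 + d gives slightly too few. The stated 220 is what the multiplication gives, so it does not quite return the 200 it was meant to protect.

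What is at stake is the accuracy of two published design figures, the power and the number expected at follow-up. The two slips are independent of each other: the beta label plays no part in the step from 200 to 220.

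**Working it through.** **Inputs, all from the sample size section:** two-sided alpha 0.05; difference 6 mmHg; 200 per level; loss 10%; target 220 per level, 110 per arm. The SD is not given, so it is back-solved below and is an assumption throughout.

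**1. Reproducing the 220**

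200 × (1 + 0.10) = 220 per level, and 220/2 = 110 per arm. This matches the stated figures exactly.

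**2. What 220 leaves at the stated loss**

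- Per level: 220 × 0.90 = 198, which is 2 short of 200.
- Per arm: 110 × 0.90 = 99.
- Loss at which 220 would leave exactly 200: 1 − 200/220 = 0.091, or 9.1%.

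**3. The exact allowance**

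- Per level: 200/(1 − 0.10) = 222.2, so at least 223.
- With equal arms: 100/0.90 = 111.1, so 112 per arm, 2 × 112 = 224 per level and 4 × 112 = 448 in total.
- Against the plan: 448 − 440 = 8 patients. The stated 220 is 2.2/222.2 = 1.0% below the unrounded figure.

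**4. Which power the 200 corresponds to**

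For two equal groups of n, the normal approximation is

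n = 2 × SD² × (z₀.₉₇₅ + z_power)² / Δ², so SD = Δ × √(n/2) / (z₀.₉₇₅ + z_power).

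With Δ = 6 and n = 200, the numerator is 6 × √100 = 60.

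| Reading | z₀.₉₇₅ + z_power | Implied SD |
|---|---|---|
| Power 0.80 (beta 0.20) | 1.960 + 0.842 = 2.802 | 60/2.802 = 21.4 mmHg |
| Power 0.20 (beta 0.80, taken literally) | 1.960 − 0.842 = 1.118 | 60/1.118 = 53.7 mmHg |

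The t-test version gives 21.36 mmHg for the first row. An SD of 53.7 mmHg would put two SDs at about 107 mmHg either side of the mean change, which is not credible for a change in systolic pressure. The first reading is the only sensible one. This is an inference from plausibility: it does not confirm that 21.4 mmHg was the value used.

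**5. Effect of 198 in place of 200**

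Power = Φ(Δ / (SD × √(2/n)) − 1.960), at the back-solved SD of 21.416:

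- n = 200: 60/21.416 = 2.802; Φ(0.842) = 80.0%.
- n = 198: 6/(21.416 × √(2/198)) = 6/2.152 = 2.788; Φ(0.828) = 79.6%.
- Difference detectable with 80% power at n = 198: 6 × √(200/198) = 6.03 mmHg.

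Solving for the SD with the t-test instead also gives 79.6% at n = 198.

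The loss in power stays small for other SDs:

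| Assumed SD (mmHg) | Power, n = 200 | Power, n = 198 | Loss (points) |
|---|---|---|---|
| 15 | 97.9% | 97.8% | 0.1 |
| 20 | 85.1% | 84.7% | 0.4 |
| 21.4 | 80.1% | 79.7% | 0.4 |
| 25 | 67.0% | 66.6% | 0.4 |

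(At the rounded SD of 21.4 the powers sit 0.1 point above those at 21.416.)

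**The case against.** The strongest reply is that none of this changes the trial. Both 200 and 10% look like rounded planning values. The gap is 2 patients per level, and a loss of 9.1% instead of 10% would close it. The uncertainty in the loss rate is larger than the difference between the two ways of allowing for it. This stands, and it is why the point is a restatement of figures and no more.

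It is also fair to say that the section never calls the 200 evaluable. Its words are "we need to enroll 200 patients to each intervention (CKD-ATSM vs. usual care and CKD-registry vs. usual care", so reading 200 as the number needed at follow-up is an interpretation. It is a safe one: the section goes on to raise 200 to 220 expressly for loss to follow-up, which makes sense only if 200 is the number wanted after loss.

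A third reply is that the 79.6% is circular, because the SD behind it was obtained by assuming 80% power at 200. That is correct. The figure shows only how far power moves between 200 and 198. It cannot show that 200 was right in the first place. The arithmetic of 220 × 0.90 = 198 needs no SD and is untouched by this, and so is the mislabelled beta.

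A reader might infer more than this from the paragraph: that the trial was really sized for 20% power, or that the beta slip fed into the 220. The documents support neither. The literal 20% requires an SD of about 54 mmHg, and 220 follows from 200 and 10% alone.

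**Conclusion.** Two separate minor errors hold as stated. The error rate should read power 0.80 (beta 0.20). The loss allowance was applied as 200 × 1.1, so at the plan's own 10% loss 220 enrolled leaves 198 per level (99 per arm), not 200.

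The size is negligible. Power falls by about 0.4 percentage points, to about 79.6%, if the unstated SD is the back-solved 21.4 mmHg, and by 0.1 to 0.4 points over an assumed SD range of 15 to 25 mmHg. The detectable difference moves from 6.00 to 6.03 mmHg on the same assumption.

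It would be tempting to conclude that the trial is underpowered or must recruit more. The documents do not support that: the target is within 1.0% of the exact figure, and nothing in the design turns on 2 patients per level. Nor can anything be concluded about whether 200 itself is right, because the article does not print the SD; the full protocol may do so.

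**What to change.** Change the wording of the sample size section in two places.

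1. Replace the beta figure with power 0.80 (beta 0.20).
2. Keep the enrolment target of 440 (220 per level, 110 per arm) and add that, with 10% loss, about 198 per level are expected at 12 months, with power marginally below 80%. If a figure is given, about 79.6% applies only if the SD is the back-solved 21.4 mmHg; the sponsor should recompute it from the SD actually used. An equivalent statement is that 220 leaves 200 if loss is about 9.1%.

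The cost is wording only. Increasing enrolment is not needed. If the sponsor nevertheless wanted the target to return a full 200, the consistent set of numbers is 112 per arm, 224 per level and 448 in total, which is 8 more patients; 223 per level does not divide equally between two arms.

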### Data analysis

Evaluation of the individual effectiveness of each intervention, as well as their additive impact, will be performed with intention to treat analyses using generalized estimating equations adjusting for patient age, clinic and preferred language, with robust standard errors to account for clustering by provider and repeated patient measures within provider. If significant differences in baseline characteristics (i.e., age, diabetes status) are found among subjects in each study arm, analyses will be adjusted for these differences using multi-variable linear regression. Additional analyses will look for evidence of effect modification by primary language and CKD severity.

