#### Patients

Prior to enrollment, using blind and secure allocation by computer, the study team randomly assigns participants to one study arm using a random number generator: CKD-ATSM or usual care. Randomization is blocked and stratified within primary care provider to increase the comparability of treatment groups and to ensure equal allocation by provider. Results are placed in a sealed randomization envelope by a study coordinator.

At the study enrollment appointment, the study team obtains written informed consent and collects baseline study measures. At the completion of this baseline visit, patients learn about their randomization assignment by opening the randomization envelope. Subjects randomized to the intervention arm are provided printed instructions about how to participate in the telephone self-management program and are guided through the process of creating a personalized log-in code for the automated telephone modules. Patients are also given a business card from his/her assigned health coach and a schedule of study events. If randomized to usual care, patients only receive a schedule of study events. All patient participants receive a $50 gift card to a local supermarket for their participation in the study.

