#### Clinical outcomes

The primary outcomes are changes in systolic BP and proportion of patients with BP control (<140/90 mmHg) after one year. The study team will measure BP using an Omron digital blood pressure monitor model HEM-907X during baseline and 12-month study visits. Per study protocol and American Heart Association guidelines, study personnel will obtain 3 BP measures in the right arm after the participant has been sitting quietly for 5 min [34]. An average of the 3 measures is recorded. Secondary clinical outcomes include: changes in urine albuminuria and weight obtained during by the study team, as well changes in eGFR, laboratory measures of metabolic bone disease (serum calcium, phosphorous, 25-OH Vitamin D and parathyroid hormone) and glycosylated hemoglobin among participants with diabetes, all ascertained through the EMR.

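### The primary model's fixed covariates omit baseline systolic BP, and the significance-triggered fallback recovers neither the lost precision nor smaller imbalances

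*Protocol article*

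**What the plan says.** All references are to the protocol article.

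- **Outcome** (Clinical outcomes): "The primary outcomes are changes in systolic BP and proportion of patients with BP control" after one year.
- **Measurement** (Clinical outcomes): the study team takes BP "during baseline and 12-month study visits", so there is one baseline and one follow-up value per patient.
- **Timing** (Enrollment and randomization, Patients): at the enrolment appointment "the study team obtains written informed consent and collects baseline study measures". The patient opens the allocation envelope only when that visit is complete.
- **Primary model** (Data analysis): "generalized estimating equations adjusting for patient age, clinic and preferred language".
- **Variance estimation** (Data analysis): the same sentence specifies "robust standard errors to account for clustering by provider and repeated patient measures within provider".
- **Further adjustment** (Data analysis): "If significant differences in baseline characteristics (i.e., age, diabetes status) are found among subjects in each study arm", the analyses are adjusted for them by linear regression. sBP is not among the examples.
- **Sample size** (Sample size considerations): 200 patients per intervention level to detect 6 mmHg by a simple t-test, "Using a two-tailed alpha of 0.05 and beta of 0.8". I read the second figure as power of 0.80. The SDs come from published trials and are not given.

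**The concern.** The covariate list is explicit, so it is a stated choice and can be judged as one. It leaves out the baseline value of the outcome itself, usually the strongest single predictor of the 12-month value. An analysis of change that does not condition on baseline carries more variance than one that does. It also keeps part of any chance baseline difference in the estimate, because patients who start high tend to fall back.

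What is at stake is precision in a trial planned at 80% power, and how the result reads if the arms happen to start apart. The baseline data are already being collected. BP control is affected too, since whether a patient ends below the threshold depends heavily on where that patient began.

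**Working it through.** **Inputs.** From the article: 6 mmHg, two-sided alpha 0.05, power 0.80, 200 per level. Assumed, because the article does not give them: the SD, the baseline-to-12-month correlation (rho), equal variance at the two visits, and a 5% level for the baseline test. The stated intra-class coefficient of 0.0008 is taken at face value, so the sums are at patient level.

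**1. The plan's own figure.** With n = 2·SD²·(1.96 + 0.8416)²/6², n = 200 requires SD = 6/(2.8016 × √(2/200)) = 21.4 mmHg. The 200 cannot be confirmed, since no SD is stated; it is consistent with 21.4. For comparison, an SD of 20 would give 175 and an SD of 22 would give 212.

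**2. Relative efficiency.** For a single-reading SD of s:
- variance of change = 2s²(1 − rho)
- ANCOVA residual variance = s²(1 − rho²)
- ratio = (1 + rho)/2

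**3. Effect on this trial, taking 21.4 as the SD of change.** Detectable difference = 6 × √ratio. Required n = 200 × ratio. Power = Φ(6/(21.4 × √ratio × √(2/200)) − 1.96).

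| rho | ratio | variance cut | detectable difference (mmHg) | n per level | power at 200 per level |
|---|---|---|---|---|---|
| change score | 1 | – | 6.0 | 200 | 0.80 |
| 0.4 | 0.70 | 30% | 5.0 | 140 | 0.92 |
| 0.5 | 0.75 | 25% | 5.2 | 150 | 0.90 |
| 0.6 | 0.80 | 20% | 5.4 | 160 | 0.88 |
| 0.7 | 0.85 | 15% | 5.5 | 170 | 0.86 |

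**4. If 21.4 is instead the SD of a single reading.** Required n per level, change score against ANCOVA, is 240 v 168 (rho 0.4), 200 v 150 (0.5), 160 v 128 (0.6) and 120 v 102 (0.7). The starting point moves, but the proportional saving is the same.

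**5. What the significance trigger leaves behind.** For an observed baseline difference D, the change-score estimate minus the ANCOVA estimate is −(1 − rho)·D. If a single reading has SD 21.4 (a separate assumption, which agrees with step 3 only at rho = 0.5), the standard error of D is 21.4 × √(2/200) = 2.14 mmHg. A difference just short of significance is then 1.96 × 2.14 = 4.2 mmHg, and no adjustment follows. The shift is 4.2 × (1 − rho) = 2.5 / 2.1 / 1.7 / 1.3 mmHg at rho 0.4 / 0.5 / 0.6 / 0.7, against a 6 mmHg target. This is the worst case under the rule, not a typical one.

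**6. The repeated-measures wording.** If both sBP values are outcomes in the GEE and each arm has its own baseline mean, the arm-by-time term is essentially the difference in mean change, so step 3 applies. If the arms share one baseline mean, the estimate behaves like ANCOVA and the loss disappears. The article does not say which is meant.

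**The case against.** **Baseline sBP may already be in the model.** With two BP visits and a GEE for repeated measures, baseline sBP may enter as an outcome, and a condensed article need not spell out the mean model. This stands in part: the loss is conditional on the arms having separate baseline means. It does not dispose of the point, because the article does name its covariates and states no shared mean.

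**The conditional rule could cover sBP.** Age and diabetes status read as examples, so a significant sBP difference would plausibly trigger adjustment. That is fair, and it would be wrong to infer that baseline sBP can never be adjusted for. But the rule does nothing when the test is not significant, and it makes the primary model depend on the data.

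**There is no validity error.** A reader might infer that the planned analysis is biased. It is not, on average, under randomisation. The shift in step 5 is conditional on the imbalance seen and is part of the sampling error that the standard error already reflects.

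**The registry contrast.** A reader might infer that baseline imbalance is likely there, because teams are randomised and provider averages run from 140 to 160 mmHg, and that registry power is below 80%. The article does not support either inference. It gives no number of teams. The sentence with that range also reports an intra-class coefficient of 0.0008, which implies almost no true difference between providers. Registry power cannot be worked out without a team count. One caution does stand: teams are randomised before patients, and the article does not say whether the registry was in use before patients' baseline visits.

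**Adjustment is not free of consequences for BP control.** With a logit link (the link is not stated), adding strong baseline predictors turns the odds ratio into a more conditional one, which changes the estimand. This stands and shapes the fix.

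**Conclusion.** The point holds as one of efficiency and pre-specification. The fixed covariates omit baseline sBP, and neither the conditional rule nor the repeated-measures wording, as written, makes up for it. Unless a common baseline mean was intended, the trial gives up 15% to 30% of the variance of its sBP comparison for rho from 0.7 to 0.4. That proportion depends on rho and on equal variances at the two visits, not on the SD. It will differ somewhat if age, clinic and language already explain part of baseline sBP.

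The absolute figures (detectable difference down from 6.0 to 5.0–5.5 mmHg, power up from 80% to about 92%–86%) rest further on 21.4 mmHg being the SD of change, which is back-solved and not stated. The change should be made, but the planned analysis would not be invalid without it.

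**What to change.** In Data analysis:

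- **sBP model:** pre-specify baseline sBP as a continuous covariate, with age, clinic and preferred language, whatever any baseline test shows. Equivalently, specify a GEE on both visits with a baseline mean common to the arms.
- **Significance trigger:** remove it. Any other prognostic covariate, such as diabetes status, should be named in advance or left to a sensitivity analysis.
- **BP control:** include baseline BP, and report a marginal (standardised) risk difference or risk ratio, so that the adjustment does not change the estimand. Its standard error should keep the clustering by provider.
- **Registry contrast:** state whether registry use began before patients' baseline visits. If it did, do not impose a common baseline mean across registry arms without justification.

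The cost is a revised model statement and a standardisation step for the binary outcome. No new measurement and no extra patients are needed, and the planned sample size can stay. The change should be fixed before outcome data are examined by arm.

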## Methods/design

### Study design

KARE is a non-blinded 2x2 factorial randomized controlled trial with two levels of randomization. Primary care providers are randomized to one of two arms: access to an electronic CKD registry or usual care. Patients are subsequently randomized to one of two arms: CKD self-management program (CKD-ATSM) or usual care. This study design, with 4 study arms, allows assessment of the individual and additive impact of both interventions (Fig. 2). Approval to conduct this study was granted by the Committee of Human Research at the University of California, San Francisco.

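### The registry is randomised by practice team but analysed with provider-clustered standard errors, which are too small for the registry effect if outcomes correlate within teams

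*Protocol article*

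**What the plan says.** The protocol article describes the unit of registry randomisation in two ways. Study design says: "Primary care providers are randomized to one of two arms: access to an electronic CKD registry or usual care". Enrollment and randomization (Providers) says that "practice teams, rather than primary care providers, are randomized to receive the CKD registry or to receive usual care", to limit contamination among clinicians. The Discussion also speaks of randomised practice teams. Teams are not single providers: "Each team consists of several physicians, nurses, nurse practitioners, medical assistants and behaviorists".

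The Data analysis section covers both interventions and their additive impact with one approach, a GEE model with patient age, clinic and language as covariates. The level at which its standard errors are clustered is the provider: "with robust standard errors to account for clustering by provider and repeated patient measures within provider". Team is not mentioned there.

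Sample size considerations reports baseline systolic BP "across primary care providers, with an intra-class coefficient = 0.0008", and on that ground uses a simple t-test calculation. It gives neither a number of teams nor a team-level ICC. Patients are randomised to CKD-ATSM in blocks, stratified within provider.

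**The concern.** All providers on a team receive the same registry allocation. A sandwich estimator clustered on provider treats them as independent replicates of that allocation, so it omits any covariance between patients of different providers on the same team. If that covariance is positive, the registry standard error is too small, its confidence interval too narrow and its test too liberal. Adjusting for clinic removes differences between clinics, but not differences between teams within a clinic.

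Within-team similarity is plausible here. The intervention works through medical assistants shared by the team and quarterly feedback addressed to the team, and the authors chose the team as the unit because they expected clinicians on a team to influence each other. The registry effect on systolic BP is one of the trial's two main comparisons, and the Discussion links positive results to dissemination in other delivery systems.

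This is not detail left to an analysis plan. The article names a specific cluster level, and that level does not match the design.

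**Working it through.** **1. The plan's own figure.** The plan has 200 evaluable patients per level of each intervention "to detect a 6-point change in systolic BP". The error rates are given as: "Using a two-tailed alpha of 0.05 and beta of 0.8". I read the latter as power 0.80. The SD is not stated, so 200 cannot be reproduced independently. Solving for it, n = 2(1.96 + 0.84)²SD²/6² = 200 gives SD of about 21.4 mmHg, and with that SD power is 0.801. This figure is not in dispute; it only sets the scale for the power column below.

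**2. Inputs.** N = 400 (2 × 200; close to 440 × 0.9 = 396). Assumed, because not stated: k = 6 to 20 teams, 5 providers per team, and team ICCs of 0.01, 0.02 and 0.05. The documented 0.0008 is also run as if it were the team ICC.

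**3. Formulas.**
- Correct design effect: D_team = 1 + (400/k − 1) × ICC.
- Design effect captured by provider clustering: D_prov = 1 + (400/(5k) − 1) × ICC.
- SE ratio: r = √(D_prov/D_team).
- True two-sided error of a nominal 5% test: 2[1 − Φ(1.96r)].

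Example with k = 12, ICC 0.01: D_team = 1 + 32.3 × 0.01 = 1.323; D_prov = 1 + 5.67 × 0.01 = 1.057; r = 0.894; true error = 2[1 − Φ(1.752)] = 8.0%.

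**4. Results by formula** (the ICC is what remains after clinic adjustment).

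| Team ICC | SE ratio, 6 / 12 / 20 teams | True error, 6 / 12 / 20 teams | Power for 6 mmHg with team-level variance, 6 to 20 teams |
|---|---|---|---|
| 0.0008 | 0.98 / 0.99 / 0.99 | 5.5% / 5.2% / 5.15% | 0.78-0.79 |
| 0.01 | 0.82 / 0.89 / 0.93 | 10.7% / 8.0% / 6.8% | 0.59-0.73 |
| 0.02 | 0.73 / 0.82 / 0.88 | 15.0% / 10.7% / 8.6% | 0.45-0.67 |
| 0.05 | 0.61 / 0.70 / 0.77 | 22.9% / 17.0% / 13.2% | 0.27-0.52 |

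The power column does not include the further loss from fewer degrees of freedom.

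**5. Simulation check.** There was no treatment effect, clinic was a fixed effect, teams were randomised within clinic, and there were 5 providers per team. About 400 patients were used (360 in the 12-team setting, through rounding), with 4,000 runs per setting. Monte Carlo error near 5% is √(0.05 × 0.95/4000), or about 0.3 percentage points. Rejection rates of the provider-clustered z-test:

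| Team ICC | 12 teams, 3 clinics | 10 teams, 5 clinics | 20 teams, 5 clinics |
|---|---|---|---|
| 0 | 5.5% | 7.5% | 5.9% |
| 0.0008 | 6.6% | 8.3% | 6.5% |
| 0.01 | 9.7% | 11.3% | 7.8% |
| 0.02 | 12.0% | 16.2% | 10.6% |
| 0.05 | 19.0% | 26.1% | 16.7% |

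The ICC = 0 row shows that part of the excess is a few-cluster effect unrelated to teams. At ICC 0.0008 the team component adds only about 0.6 to 1.1 points.

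**6. Check of the remedy.** In the same runs an uncorrected team-clustered z-test rejected in about 12% to 29% of null trials. A team-level t-test with clinic terms rejected in about 4% to 6%.

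**The case against.** The best defence is the documented ICC. Providers are nested in teams, so between-team variance is part of between-provider variance. For baseline systolic BP, the team ICC can therefore hardly exceed 0.0008. At that value the error is slight, and an assumed 0.01 or 0.05 is about 12 or 60 times larger. The article also says that patient demographics are similar across teams within a clinic, and the model adjusts for clinic, which makes large residual team ICCs harder to defend.

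Most of this stands as to size. It rules out presenting the upper rows of the tables as expected values; they are sensitivity assumptions. It does not settle the matter. The 0.0008 describes baseline systolic BP by provider. It is not a team-level ICC, and it does not describe 12-month change or BP control, the other primary outcome, during a year of an intervention delivered by teams. Teams that use the registry to different degrees could create correlation that was absent at baseline.

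It may also be said that the choice of small-sample correction belongs in an analysis plan. That is fair for the particular estimator, but not for the cluster level, which the article states.

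The Study design sentence might be read as making the provider the unit, in which case the planned clustering would match. The Enrollment section expressly rules that reading out, so the sentence needs rewording and does not rescue the analysis.

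**Conclusion.** The mismatch is certain: the team is randomised, the provider is the cluster, and nothing in the model represents the team. The direction is also clear if within-team correlation is positive. The size is not known. It runs from negligible (about 5.15% to 5.5% by formula at the documented ICC; about 6.5% in the simulated 12- and 20-team settings and 8.3% with 10 teams in 5 clinics, mostly a few-cluster effect) to serious (13% to 23% by formula at an assumed team ICC of 0.05). All of these figures rest on the assumed 6 to 20 teams and 5 providers per team.

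A reader might infer that the registry result will be declared significant too often, or that the false-positive rate is in fact two to five times nominal. The documents do not support that, because they give no team ICC and no number of teams, and the one ICC they report points to a small effect. Nor does the problem reach the CKD-ATSM comparison. The contrast of both interventions with neither is exposed in principle, but it uses about half the patients in each team, so the rates above do not carry over to it and were not computed for it.

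**What to change.** In Data analysis, state that every comparison involving the registry accounts for clustering at practice-team level, with providers and patients nested in teams, and uses a small-sample method. Suitable choices are a bias-corrected sandwich (for example Mancl-DeRouen or Kauermann-Carroll) with t degrees of freedom based on the number of teams, or a team-level or permutation test. Changing the cluster identifier alone is not enough, because the uncorrected team-clustered z-test is itself anti-conservative with few teams. Provider clustering can stay for CKD-ATSM. Reword the Study design sentence so that it agrees with the Enrollment section that practice teams are randomised.

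No new patient data are needed, only a team identifier and revised wording. The cost is wider registry intervals. In a team-level analysis with clinic terms the degrees of freedom are teams − clinics − 1: 20 − 5 − 1 = 14, 12 − 3 − 1 = 8, or 10 − 5 − 1 = 4. The t critical values are then about 2.14, 2.31 and 2.78 in place of 1.96. That widening reflects the number of units actually randomised. If team correlation proves negligible, the standard error itself should change little.
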